### Primary Outcome is HRQoL:^13^

It is a multidimensional concept that describes individuals or groups’ perceived physical and mental health over some time. The primary outcome changes in HRQoL which will be assessed by validated disease-specific (MacNew quality of life after myocardial infarction (MacNew QLMI) form)^14^ and generic instruments (Short Form 12 (SF-12)).^15^

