***ASSESSMENTS:***					
*Basic Demographic Variables*		X			
HRQoL (MacNew QMLI & SF-12)		X		X	X
*Clinical Outcomes*		X		X	X
*Behavioural Outcomes*		X		X	X
*Adherence*					X

This will be a single-centre, single-blinded, two-arm randomised controlled trial conducted at Armed Forces Institute of Cardiology (AFIC). The clinical trial is registered with the Australian New Zealand Clinical Trials Registry (ANZCTR) under trial identity number ACTRN12619001731189.^9^

The total study duration will be approximately two years from January 2019 till December 2020. After analysing hospital data, it is expected that patient recruitment will take approximately 16-20 weeks (at least 10-12 patients per week) while intervention will take 23-24 weeks.

The patient coming to AFIC emergency and admitted in its wards with ACS diagnosis with ACS will be enrolled in this clinical trial after fulfilling the eligibility criteria as in Table-II. ACS will be diagnosed by at least one on-call cardiologist (cardiac consultant) based on the chest or epigastric pain, radiating to the arm, jaw, neck or back), cardiac markers ((Creatine phosphokinase and/or creatine kinase-MB and/or Troponin I)) and/or electrocardiogram (ST elevation or non-ST elevation).

**Table II T2:** Inclusion and exclusion criteria for MCard

Inclusion criteria	Exclusion criteria
i.Age eligibility: From 35 years till 65 years.	i.Mini-mental State Examination of less than 24.
ii.Gender eligibility: Both	ii.Not physically or mentally capable of handling a mobile phone.
iii.Diagnosed with documented ACS evidence by a cardiologist based on the chest or epigastric pain, radiating to the arm, jaw, neck or back and/or cardiac markers and/or electrocardiogram.	iii.Diagnosed with familial hypercholesterolemia.
iv.Ejection fraction of >25%.	iv.History of cerebrovascular accident.
v.Patients are having mobile phone ownership or a caretaker who can assist in handling mobile.	v.Patient on hemodialysis or peritoneal dialysis.
vi.Patients are giving fully informed voluntary written consent for participation.	vi.A patient diagnosed with hepatitis B or C by serology.
vii.The patient may only have received medical treatment or may have undergone cardiac revascularisation procedure percutaneous coronary intervention or thrombolytic therapy.	vii.Concurrent severe disease, such as malignancy.
	viii.Is or may be pregnant.

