The primary outcome measure that is HRQoL physical component summary was used for sample size estimation in STATA version 14. A sample size of 61 per group in a ratio of 1:1 was calculated by two independent mean tests of SF-36 physical component (control group; 39.09 and intervention group 42.65),^10^ assuming SF-36 physical component variability of 6.74 and 7.14 in control and intervention group respectively, a power of 80% and a significance level of 5%. To allow for a predicted 25% drop-out or lost to follow-up rate from adverse events, the sample size has been increased to 80 per group, recruiting 160 participants (80 x 2=160) altogether.

After recruitment into the clinical trial, the baseline information will be recorded by a data collector. The data collector will be blinded to the participant’s actual trial arm before and after the intervention. The random assignment of recruited participants into the two arms was performed by a research associate using web-based permuted block randomisation (4 x 8), ensuring 1:1 ratio between the two arms (i.e. 80 in each). Allocation concealment will be conducted by the sequentially numbered opaque sealed envelope.

The data collector will be communicating with the participants (intervention and control group) for the follow-up data collection at 12 weeks and 24 weeks. Participants will be requested not to disclose their counselling session or text message communication to the data collector. At 12 and 24 weeks, the participants will be asked for a follow-up to the hospital. If the patient cannot come for follow-up, the information will be collected via telephone interview within the ± 01 week period of 12 or 24 weeks.

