Data will be entered and analysed in STATA version 14 using the intention to treat principle. Descriptive data will be presented as frequency and percentages. Continuous data will be presented by means with their 95% confidence intervals. Table and graphs will be constructed for reporting sociodemographic, behavioural and clinical data. Age, gender, education level, comorbidity will be included as potential covariates. All of the analyses will be taken statistically significant at a two-tailed p-value of < 0.05.

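### The sample-size paragraph and the outcome section name different primary outcomes, and the stated 5% and 80% hold only if one score at one visit is primary

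*Protocol article*

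**What the plan says.** Four places in the protocol article bear on this.

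- **Methods, sample-size paragraph.** "The primary outcome measure that is HRQoL physical component summary was used for sample size estimation in STATA version 14". The calculation compares two means of the SF-36 physical component, with "a power of 80% and a significance level of 5"%. It gives 61 per group, raised to 80 for drop-out.
- **Primary Outcome section.** "The primary outcome changes in HRQoL which will be assessed by validated disease-specific" (MacNew QLMI) and "generic instruments (Short Form 12 (SF-12")). No score, domain or component is singled out, and no time point is given.
- **Table-I and the follow-up paragraph.** The row "HRQoL (MacNew QMLI & SF-12") is marked at baseline, 12 and 24 weeks. The data collector contacts both groups "for the follow-up data collection at 12 weeks and 24 weeks". Neither visit is called primary.
- **Data-analysis paragraph, after Secondary Outcomes.** "All of the analyses will be taken statistically significant at a two-tailed p-value of < 0.05". No ordering of outcomes and no adjustment is mentioned.

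**The concern.** The two statements of the primary outcome cannot both stand. One is a single physical score. The other is change in HRQoL on two instruments, and one of these, MacNew, does not appear in the sample-size paragraph at all.

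The significance level and power in the sample-size paragraph belong to one test. They carry over to the trial's conclusion only if that conclusion rests on one score at one visit. If success could come from whichever instrument or visit is significant, the chance of a false claim exceeds 5%. If both instruments must succeed, power falls below 80%. The article does not say which applies, so a reader of the results could not tell whether the headline HRQoL result was the one planned. This matters because the abstract proposes scaling MCard up to other cardiac centres if it proves effective.

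**Working it through.** **1. Inputs from the sample-size paragraph.** Means 39.09 (control) and 42.65 (intervention), so the difference is 3.56. SDs are 6.74 and 7.14, so the root mean square SD is √((6.74² + 7.14²)/2) = 6.943. Alpha is 0.05, power 80%, allocation 1:1, drop-out 25%.

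**2. Reproducing the plan's figure.** n per group = 2·SD²·(z₀.₉₇₅ + z₀.₈₀)²/difference² = 2 × 6.943² × (1.960 + 0.842)²/3.56², which rounds up to 60. The unequal-variance t-test gives 79.5% power at 60 and 80.2% at 61, so the stated 61 reproduces. A one-sided test would need 48, so the figure is two-sided. For drop-out, 60/0.75 = 80 and 61/0.75 = 81.3, close to the stated 80. The sizing is therefore for exactly one two-sided 5% test.

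**3. Number of possible primary tests.** The outcome section gives at least two (one per instrument). The schedule makes four possible (two instruments × two visits). Treating both visits as tests is an assumption, because the schedule only says when data are collected.

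**4. False-positive rate if any one result were enough.** With k independent tests the rate is 1 − 0.95^k. Correlated tests were evaluated as equicorrelated normal statistics. The correlations are assumed.

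| Tests | Independent | ρ=0.3 | ρ=0.5 | ρ=0.7 | ρ=0.8 |
|---|---|---|---|---|---|
| 1, two-sided | 5.0% | – | – | – | – |
| 2 (two instruments, one visit), two-sided | 9.8% | 9.5% | 9.1% | 8.4% | 7.8% |
| 4 (two instruments, two visits), two-sided | 18.5% | 17.4% | 15.6% | 13.0% | 11.4% |
| 4, favouring MCard only | 9.6% | 8.7% | 7.8% | 6.5% | 5.7% |

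The comparator for the last row is 2.5%, the chance that a single two-sided 5% test falsely favours MCard.

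**5. Power if both instruments had to succeed at one visit.** Assume MacNew has the same standardised effect as the physical component, 3.56/6.943 = 0.513. The expected z-statistic is 0.513/√(2/n): 2.81 at n = 60 and 2.83 at n = 61. The probability that both exceed 1.96 is:

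- ρ = 0.5: 69.0% (n = 60) and 69.9% (n = 61)
- ρ = 0.7: 71.5% (n = 60) and 72.4% (n = 61)

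**6. Cost of keeping four either-or primaries.** Bonferroni gives 0.05/4 = 0.0125 per test. The formula in step 2 then needs 85 evaluable per group, and 85/0.75 = 113.3, so 114 recruited per group. With 61 evaluable, power per test falls from 80.8% (normal approximation) to 63.1%.

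**The case against.** The strongest reply is that the sample-size paragraph settles the matter. It uses the term primary outcome for one score, the outcome section describes the broader construct and its instruments, and SF-12 can supply a physical component summary. On that reading one test remains. This narrows the gap but does not close it: MacNew is still listed as a primary measure, so the outcome section would still need correcting.

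A second reply is that this is a condensed article, and that time point, hierarchy and multiplicity method may sit in a fuller protocol or analysis plan. That is fair, and the absence of a multiplicity method is not the point here. Two incompatible statements of the primary outcome within one text are not an omission, because any later plan must depart from one of them.

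A reader might go further and infer that the plan lets any one significant HRQoL result make the trial positive, or that the outcome section makes both visits primary. The text supports neither. The analysis paragraph sets a threshold and not a success rule, and the outcome section is silent on timing; the two visits come only from the assessment schedule. Nor should 18.5% be quoted as the trial's error rate. It requires four independent tests, which is implausible for HRQoL scores from the same patients, and it counts errors in both directions.

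**Conclusion.** The contradiction is in the current text and should be resolved. The sample-size arithmetic is sound, but it describes a single-test trial that the outcome section does not describe. How far the error rate or power departs from 5% and 80% depends on a success rule that is not written and on correlations that are not given, so the figures are a conditional range:

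- **Any one result enough:** about 8-10% two-sided with two instruments at one visit, and about 11-17% with two instruments at two visits. In favour of MCard, the latter is about 6-9% against 2.5%.
- **Both instruments required at one visit:** power of about 69-72% instead of 80%, resting also on an equal effect on MacNew, for which the article offers no figure.
- **One score at one visit:** no inflation and no loss of power.

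**What to change.** Reconcile the sample-size, primary-outcome and data-analysis paragraphs around one primary endpoint. The natural choice is the SF-12 physical component summary, tested at two-sided 0.05 at one stated visit, for example 24 weeks, the end of the intervention. The sample-size paragraph uses SF-36 values while the trial collects SF-12, so it should say that the SF-12 score is the collected counterpart of the score used for sizing.

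Make MacNew, the SF-12 mental score and the other visit secondary. Report them as estimates with 95% confidence intervals, or test them in a fixed order only after the primary succeeds. Limit the p<0.05 declaration in the data-analysis paragraph accordingly.

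The cost is wording: no extra patients or data, and the sample size stays at 61 (80 recruited) per group. The downside is that a MacNew or 12-week result could no longer carry the headline claim alone. If the investigators want all four comparisons as either-or primaries, the Bonferroni figures in the working show what that would require.

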### Secondary Outcomes:

***Clinical Outcomes:*** Clinical outcomes are quantifiable changes in physical health as a result of health care interventions. In this randomised control trial, the following clinical outcomes will be recorded:
***Physiological parameters:**** Blood pressure measurement (systolic and diastolic in millimetres of mercury) will be taken according to the Centers for Disease Control and Prevention.* Body mass index measurement will be derived from weight in kilogram divided by height in meters squared.The number of days of current hospitalisation at 12 and 24 weeks if any.Number of readmissions to the hospital within 180 days after ACS date.Major adverse cardiovascular events (MACE): After hospital discharge, if patients come to the hospital with repeat-MI, heart failure, symptom-driven coronary revascularisation or death, they will be identified as having a MACE.
***Behavioural outcomes:*** It refers to the end result of action to improve their health. The following patient behavioural outcomes will be assessed on the subjective basis within the last four weeks:
Self-monitoring (systolic and diastolic blood pressure in millimetres of mercury and body weight in kilogram at least once weekly)Number of steps taken per day measured by pedometer (Physical activity)***Medicine compliance:*** Taking medicines according to their cardiologist prescription.***Salt restriction:*** Subjective patient salt intake will be recorded. They will be asked if they think they are taking less than one teaspoon per day in all food.***Smoking status (no smoker, current smoker or ex-smoker):*** Smoking status of the patient’s last month will be recorded.***Healthy diet preferences:*** Subjective patient healthy diet will be recorded. They will be asked what type of food they prefer. Are they following the recommended diet?***Acceptability:*** At the end of the clinical trial, at 24 weeks, the post-ACS patient will be asked to judge the program acceptability on a Likert scale from 1 to 5, 1 being unacceptable and 5 being acceptable.

Data will be entered and analysed in STATA version 14 using the intention to treat principle. Descriptive data will be presented as frequency and percentages. Continuous data will be presented by means with their 95% confidence intervals. Table and graphs will be constructed for reporting sociodemographic, behavioural and clinical data. Age, gender, education level, comorbidity will be included as potential covariates. All of the analyses will be taken statistically significant at a two-tailed p-value of < 0.05.

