### Intervention Group:

MCard will be a medically supervised cardiac rehabilitation program for a total period of 23-24 weeks for the intervention group. The Phase-I will be initiated during the hospital stay and will include one individual face to face behavioural change modification counselling using HEARTS, a technical package for cardiovascular disease management by the World Health Organization.^11^ Phase-II will be initiated after hospital discharge. The intervention details are devised in line with Tidier guidelines^12^ and are attached as supplementary file 2. The details of the groups are described in Table-III.

**Table III T3:** Detail of the cardiac rehabilitation intervention of the two groups

	Phase I (During hospital stay)			Phase II (After discharge)

	Standard post-ACS care	Empowering with self-monitoring devices	Behaviour change modification counselling	Mobile Text communication
Group A (n=80, control)	√	√		
Group B(n=80, intervention)	√	√	√	√

The core component of the MCard is that the participants will receive the same standardised messages on their mobile phones related to healthy lifestyle modification through a specifically designed software. This will be two-way communication in which the patient will receive text messages and inquire info through texting back. A health professional (principal investigator) and / or an associate researcher will be receiving the calls and messages from the patients and respond to them. The mobile text messages will be the same for all the intervention group. Manually one message per day will be communicated to group B for 23-24 weeks. The principal investigator will communicate a total of 161-168 messages through the MCard designed software. The health messages have been devised by first having a small group discussion with patients to identify the gap in knowledge related to modifiable risk factors (physical inactivity, unhealthy diet, salt intake, tobacco use and medicine defiance). The devised messages were rephrased for communication after having a consultation with a cardiologist. Rephrasing of the messages was conducted for easy understanding of the participants.

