### Control Group:

The control group will receive standard care. However, they will not receive text messages on their mobile related to healthy lifestyle modifications.

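### MACE is counted only when the patient comes to the hospital, so deaths outside hospital, and probably events treated elsewhere, are not counted

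*Protocol article*

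**What the plan says.** Under Secondary Outcomes, MACE is listed among the clinical outcomes. After discharge, "if patients come to the hospital with repeat-MI, heart failure, symptom-driven coronary revascularisation or death, they will be identified as having a MACE". No other sentence defines a MACE. The sentence does not name the hospital, but the Methods describe a single-centre trial at one cardiac institute.

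Follow-up is the same for both arms. Table I schedules clinical outcomes at baseline, 12 and 24 weeks. The follow-up paragraph in Methods (after Table II) has a data collector, meant to be blinded, contact both groups at 12 and 24 weeks. It adds: "If the patient cannot come for follow-up, the information will be collected via telephone interview". The section on self-monitoring devices repeats the telephone fallback.

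Other contact differs by arm. Under Intervention Group: "Manually one message per day will be communicated to group B for 23-24 weeks". Patients may also text back or call: "A health professional (principal investigator) and / or an associate researcher will be receiving the calls and messages from the patients". Under Control Group, participants have standard care and "they will not receive text messages on their mobile related to healthy lifestyle modifications". Table III shows mobile text communication for Group B only.

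**The concern.** A composite that names death as a component should count every death. Here attendance at the hospital is part of the definition, so the patients with the worst outcome, those who die before reaching it, can drop out of the endpoint. Events treated at another hospital probably drop out too. What is at stake is an undercounted secondary endpoint that would be reported as MACE including death.

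There is a lesser worry. When an endpoint depends on attendance, anything that changes attendance in one arm changes the count in that arm. Group B has continuing contact with the study team and Group A does not.

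**Working it through.** **1. The rule applied to types of event.** The hospital can be read as the trial centre (the natural reading in a single-centre trial) or as any hospital.

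| Event after discharge | Trial centre only | Any hospital |
|---|---|---|
| Repeat MI, heart failure or revascularisation at the centre | counted | counted |
| The same at another hospital | not counted | counted |
| Death at home or otherwise outside hospital | not counted | not counted |

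The third row fails on both readings. The second depends on the reading.

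**2. Whether the scheduled contacts close the gap.** Table I says when clinical outcomes are assessed; the MACE sentence says what counts. An MI treated elsewhere and reported by telephone at 12 weeks would be known, yet would not meet the rule if the hospital is the centre. The fallback is an interview with the patient, which cannot establish a death. The sample-size paragraph predicts 25% drop-out or loss, attributed to adverse events: 0.25 × 80 = 20 patients per arm. These are patients whose MACE status matters.

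**3. Size if capture is equal in the two arms.** The documents give no MACE rate, capture rate or MACE power, so there is no plan figure to reproduce and every rate below is an assumption. Recorded events per arm = n × p × c, with n = 80 (from the plan), true 24-week rate p and captured fraction c.

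| p | c = 1 | c = 0.70 |
|---|---|---|
| 10% | 80 × 0.10 = 8.0 | 5.6 |
| 15% | 80 × 0.15 = 12.0 | 8.4 |
| 20% | 80 × 0.20 = 16.0 | 11.2 |

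The risk ratio is unbiased because c cancels. Events, and so precision, are lost.

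**4. Size if capture differs by arm.** Observed risk ratio (B/A) = true risk ratio × c_B / c_A. With a true ratio of 1:

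| Captured fractions | B the higher | A the higher |
|---|---|---|
| 0.95 and 0.80 | 0.95/0.80 = 1.19 | 0.80/0.95 = 0.84 |
| 0.90 and 0.70 | 0.90/0.70 = 1.29 | 0.70/0.90 = 0.78 |
| 0.90 and 0.60 | 0.90/0.60 = 1.50 | 0.60/0.90 = 0.67 |

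At p = 15% with 0.90 in B and 0.70 in A, the recorded events are 80 × 0.15 × 0.90 = 10.8 and 80 × 0.15 × 0.70 = 8.4, a gap of 2.4. The standard error of the log risk ratio is √(1/10.8 − 1/80 + 1/8.4 − 1/80) = 0.432. The approximate 95% interval around 1.29 is therefore 0.55 to 3.0. Such a distortion would be hard to see in the data. The table shows a range in both directions and estimates nothing about this trial.

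**The case against.** The best defence is that the sentence is loosely worded. Nobody comes to a hospital with death, so it may simply list components, and a condensed article may leave vital-status checks, outside records and adjudication to the full protocol. It is true that their absence here is no finding. But the attendance condition is stated, not omitted. It is the only definition given, and whoever follows it leaves out deaths outside hospital.

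It can also be said that MACE is a clinical outcome and that clinical outcomes are already assessed at 12 and 24 weeks in both arms, with a telephone fallback. That stands, and it makes the repair cheap. It does not cure the rule, which is not tied to those contacts.

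A reader might go further and infer that Group B's events will be captured more fully, so that the programme will look harmful, with a risk ratio near 1.29. The documents do not support this:

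- Both arms have the same scheduled assessments, by a data collector meant to be blinded, and participants are asked not to reveal their counselling or messages.
- Nothing says that the message line feeds MACE recording or sends patients to the hospital. The line is described as lifestyle messages with a chance to ask for information: "This will be two-way communication in which the patient will receive text messages and inquire info through texting back".
- Under the rule as written, an event learned of by text adds no MACE unless the patient also attends. The remaining route is a change in attendance, which could go either way: contact might prompt attendance, or advice given on the line might reduce it.

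**Conclusion.** The point holds for the definition. As written, deaths outside hospital are excluded from a composite that names death, whichever hospital is meant. Events treated elsewhere are probably excluded too, on the reading that the hospital is the trial centre. The number lost cannot be derived from the documents; under the assumed rates above with 70% capture, it is 2.4 to 4.8 events per arm (8.0 − 5.6 to 16.0 − 11.2).

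Unequal capture is a possible consequence of an attendance-based endpoint combined with a contact line in one arm. It is an inference of unknown direction and size, and no risk ratio should be attached to it except as illustration. Nor does it follow that the MACE comparison must be biased: with equal capture, the risk ratio is unbiased and only events are lost.

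MACE is a secondary outcome, so the primary health-related quality of life comparison and its sample size are unaffected. The definition should be corrected, but the trial does not depend on it.

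**What to change.** Redefine MACE as repeat MI, heart failure, revascularisation driven by symptoms, or death from any cause, wherever it occurs, from discharge to the 24-week contact. Keep the post-discharge start. Phase I counselling takes place in hospital after allocation, so a clock started at randomisation could count procedures from the index stay.

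Ascertain it in both arms with the same questions at the existing 12- and 24-week contacts, asking next of kin when the patient cannot be reached, and check hospital records where available. An event first heard of through the message line should count only once confirmed by that common route, so that the line itself cannot create a difference between arms.

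The cost is a few questions at contacts already planned, some calls to next of kin, and record checks. A small downside is that some events treated elsewhere will rest on report rather than on hospital records.

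### The named covariates leave out the baseline HRQoL score, which is collected in both arms; adding it gains precision at almost no cost

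*Protocol article*

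**What the plan says.** The analysis paragraph at the end of Methods, just before the ethics section, commits to intention to treat and a two-sided 5% level, and says that "Age, gender, education level, comorbidity will be included as potential covariates". It names no model, dependent variable or time point.

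The section on the primary outcome reads "The primary outcome changes in HRQoL which will be assessed by validated disease-specific" and goes on to name MacNew QLMI and SF-12. The row of Table-I labelled "HRQoL (MacNew QMLI & SF-12)" is marked at baseline, week 12 and week 24, so each participant in both arms should have a baseline score.

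The sample-size paragraph compares score levels, not changes: "two independent mean tests of SF-36 physical component (control group; 39.09 and intervention group 42.65)", "assuming SF-36 physical component variability of 6.74 and 7.14 in control and intervention group respectively", with "a power of 80% and a significance level of 5%". It claims no gain from baseline adjustment.

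**The concern.** A participant's own baseline score is likely to be the strongest predictor of the follow-up score among the variables this trial measures. The article lists its adjustment variables, and that one is absent. An analysis plan that followed the list as written would use baseline only through subtraction (a change score) or not at all (a raw follow-up score). Neither is as precise as adjusting for it.

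The choice matters more if the correlation is modest. Baseline is taken before discharge from the ACS admission and the last assessment is 24 weeks after discharge, so a modest correlation is plausible, though the article neither gives nor implies a value. With a low correlation, the change in a score varies more than the score itself, and the sample size was computed from the SD of the score.

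What is at stake is power for the primary outcome and the sensitivity of the estimate to a chance difference between the arms at baseline.

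**Working it through.** **Inputs from the sample-size paragraph.** Means 39.09 and 42.65, so the difference is 3.56. SDs 6.74 and 7.14, so the common SD is √((6.74² + 7.14²)/2) = 6.94. Two-sided 5%, 80% power. There are 80 per arm with 25% loss, so 80 × 0.75 = 60 completers per arm.

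**Assumed.** The baseline-to-follow-up correlation r (0.3, 0.5 and 0.7 shown); equal SDs at baseline and follow-up; the SF-36 physical component figures carried over to the HRQoL score analysed; no allowance for the four named covariates.

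**The plan's own figure.** A two-sample comparison of means needs 60 per group by the normal approximation and 61 by the noncentral t (power 80.2% at 61). The stated 61 reproduces. At 60 completers per arm, power is 79.5%.

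**Formulas.**
- Raw follow-up score: SD = 6.94, whatever r is.
- Change score without baseline as a covariate: SD = 6.94 × √(2(1 − r)).
- Baseline-adjusted (ANCOVA): SD = 6.94 × √(1 − r²).
- Standard error = SD × √(2/60); power from the noncentral t with noncentrality 3.56/SE.

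**Results at 60 per arm.**

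| r | SD, change | SD, adjusted | Power, change | Power, raw follow-up | Power, adjusted |
|---|---|---|---|---|---|
| 0.3 | 8.21 | 6.62 | 65% | 80% | 83% |
| 0.5 | 6.94 | 6.01 | 80% | 80% | 90% |
| 0.7 | 5.38 | 4.96 | 95% | 80% | 97% |

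The first row worked through: the change score has SE 8.21 × √(2/60) = 1.50 and noncentrality 3.56/1.50 = 2.37. The adjusted analysis has SE 6.62 × √(2/60) = 1.21 and noncentrality 2.94.

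**Crossover.** The change score matches the raw follow-up score when 2(1 − r) = 1, that is, at r = 0.5, and is worse below it. The adjusted variance divided by the change-score variance is (1 − r²)/(2(1 − r)) = (1 + r)/2, which never exceeds 1. Against the raw score the ratio is 1 − r², which also never exceeds 1. Apart from one degree of freedom, adjustment is never less precise than either alternative.

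**Chance imbalance.** If the baseline SD is also 6.94, the baseline difference between arms has a standard deviation of 6.94 × √(2/60) = 1.27 points over repeated randomisations. Given an observed baseline difference D, the expected shift in the treatment estimate is −(1 − r)D for a change score, rD for a raw follow-up score and zero for ANCOVA. For D = 1.27 and r = 0.3, the shift is 0.7 × 1.27 = 0.89 points in size for the change score (25% of 3.56) and 0.3 × 1.27 = 0.38 points for the raw score (11%). At r = 0.7 the two sizes swap.

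**The case against.** The strongest reply is that the article never states an unadjusted change-score analysis. It names no model, calls its covariates potential, and does not say that the list is complete. Describing the outcome as a change does not exclude ANCOVA: regressing change on arm and baseline gives the same treatment effect as regressing the final score on arm and baseline. A fuller analysis plan, not shown here, may include the baseline score. This stands in part. It rules out saying that the trial will be analysed inefficiently. It does not remove the point that the article names adjustment variables and omits the one most worth having.

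Four stronger readings are tempting, and the documents do not support them.

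- A reader might infer that the stated 80% power is wrong. It is not: 61 per group reproduces for the unadjusted comparison of means that it describes.
- A reader might infer that the trial is underpowered for its declared outcome. That requires an unadjusted change score and r below about 0.5. The article states neither.
- A reader might infer that baseline imbalance is left uncorrected. That describes a raw follow-up comparison. A change score does use baseline, and over-corrects when r is below 1.
- A reader might infer a biased trial. Under randomisation both unadjusted estimators are unbiased on average. The shift arises only given a chance imbalance, and none has been shown.

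The size of the gain also depends on r. At r = 0.7 the advantage over a change score is about 2 percentage points of power, although the advantage over a raw follow-up score is then about 18 (97.4% against 79.5%).

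**Conclusion.** The point holds as a missed gain in precision. It is not an error in the sample size and does not show bias. For a primary outcome of change, with baseline measured in both arms, the named covariates omit the baseline score. At 60 completers per arm, adjusting for it raises power from 65–95% (change score) or about 80% (raw follow-up score) to 83–97% as r runs from 0.3 to 0.7. It also removes, in expectation, the shift from a chance baseline difference.

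These figures rest on the article's difference and SDs, equal SDs at baseline and follow-up, and an assumed r. The direction does not depend on r: apart from one degree of freedom, adjustment is never the less precise choice. Because the change costs almost nothing, it should be made before the data are analysed.

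**What to change.** In the analysis paragraph, add the baseline value of the same HRQoL score as a prespecified covariate in the model for 24-week HRQoL. This can be an ANCOVA of the week-24 score on arm and baseline, or a repeated-measures model over weeks 12 and 24 with baseline as a covariate. Do this separately for each HRQoL score, always using that score's own baseline. Treat other continuous outcomes measured at baseline, such as blood pressure and BMI, in the same way.

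The cost is a change of analysis wording and one degree of freedom per model. No new data, visits or participants are needed, and the sample size can stay as stated.
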